### Renal fibrosis

One of the most common causes of graft failure after transplantation is the development of chronic allograft nephropathy.^20^ The aim of this study is to determine if EVNP can slow the progression of fibrosis. Biopsies of the kidney will be taken pretransplant and after 3 months. Biopsies will be fixed in formalin and paraffin embedded cut sections of the graft will be stained with sirius red (stains for collagen III). The degree of fibrosis will be quantified using computerised digital image analysis.

### Injury markers

Ischaemia reperfusion injury is a leading cause of early graft dysfunction. The aim of this study is to determine if EVNP can reduce the amount of inflammation and injury after transplantation. Blood and urine samples will be collected pretransplant and post-transplant and used to measure inflammation (inflammatory cytokines: interleukin-6 (IL-6), tumour necrosis factor-α, IL-8) and kidney injury (neutrophil gelatinase-associated lipocalin, liver fatty acid binding protein). Further biopsies of the kidney will be taken and snap frozen in liquid nitrogen or stored in RNA later, preimplantation and 30 min post-transplant. These will be used for light microscopy and RNA sequencing to determine the degree of acute tubular injury, measure inflammatory cytokines and downstream signalling molecules such as vascular endothelin growth factor (VEGF) and Erythropoietin (EPO).

### Sample storage

Samples will be stored in the clinical and research laboratories within the participating centres. Samples will be coded and donor identifiable material will only be available to the principal investigator (PI) and the research team at the participating centres. Samples are appropriately labelled in accordance with the trial procedures to comply with the 1998 Data Protection Act. Biological samples collected from participants as part of this trial will be transported, stored, accessed and processed in accordance with national legislation relating to the use and storage of human tissue for research purposes and such activities shall at least meet the requirements as set out in the 2004 Human Tissue Act and the 2006 Human Tissue (Scotland) Act.

On completion of the trial, samples will be disposed of in accordance with the Human Tissue Authority's Code of Practice.

### Statistics

#### Sample size determination

The trial size was calculated with respect to the primary end point, which is DGF defined as the requirement for dialysis in the first 7 days post-transplantation. Based on 5 years of data from the three participating centres, the overall rate of DGF in DCD kidney transplants is 50%. In a pilot series of kidney transplants from extended criteria donors (ECD), 18 kidneys undergoing CS followed by 1 hour of EVNP were compared with a historical control group of 47 ECD transplants after CS alone. The DGF rates were 1/18 (6%) in the EVNP group compared with 17/47 (36%) in the CS group.^14^

Using a fixed sample size study, with interim analyses after 125 and 250 patients have been enrolled and reached 365 days post-transplant, a total of 376 patients receiving a DCD kidney (Maastricht categories III and IV controlled donors) will be required to detect a 30% relative reduction in DGF (from 50% to 35%) with a power of 80% and a statistical significance of α=0.05. To allow for a study withdrawal rate of 6%, a total of 400 patients will be recruited.

#### Interim analysis

Two interim analyses will be performed during the study period. The first of these will be after 125 patients have received a transplant and reached 7 days post-transplant and the second after 250 patients have been recruited (and have received a transplant and reached 7 days post-transplant).

#### Analysis population and principles

The population used for efficacy analyses will be an intent-to-treat population including all eligible randomised patients. This will be the primary analysis for the trial. Characteristics of all randomised patients will be tabulated by arm of the trial to describe the cohort.

The primary and secondary outcomes will also be analysed per protocol.

### Analysis of primary and secondary outcomes

The analyses will be described in detail in a full statistical analysis plan. This section summarises the main issues. A full statistical analysis plan will be drawn up prior to the first interim analysis.

#### Primary analysis

The number of patients who experience DGF between the two groups will be compared using a logistic regression model adjusting for cold ischaemic time and donor age.

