### Eligibility

Patients will be eligible for the trial if they meet the following criteria: patients undergoing a DCD kidney transplantation (Maastricht categories III and IV); the donor and recipient must be ≥18 years and it must be the patient's first or second kidney transplant.

Written informed consent will be taken from all patients included in the trial by a qualified member of the study team. Patients will not be eligible if the donor or recipient is under the age of 18 years, the DCD donor is in Maastricht categories I and II, patients receiving a third or subsequent kidney transplant, patients receiving multiorgan transplants, for example, simultaneous pancreas–kidney transplantation, patients receiving dual kidney transplants, paediatric en-bloc kidney transplants or kidneys that have been preserved by hypothermic machine perfusion. There will be four participating centres in the UK: Cambridge (lead), Newcastle, Guy's and Edinburgh.

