### Randomisation

Patients will be allocated at random in a 1:1 ratio to either static cold storage (CS) plus 1 hour of EVNP (n=200) or CS (n=200) only. A patient information sheet will be given to potential recruits on admission for DCD kidney transplantation and written informed consent will then be obtained (see online supplementary appendices 1 and 2). Randomisation will be performed after the transplant recipient and kidney have both arrived in the transplanting centre and a final decision to proceed with transplantation has been made by a member of the study team. The randomisation will be performed on a web-based system (sealed envelope) which uses a computer-generated randomisation sequence. In cases where paired kidneys from the same donor are transplanted in the same centre, one kidney from the pair will be randomly allocated to CS and the other to EVNP. In these cases, the randomisation will also determine which kidney (right or left) will be transplanted first. Owing to the nature of the trial, no one is blinded to treatment allocation.

10.1136/bmjopen-2016-012237.supp1supplementary appendix

10.1136/bmjopen-2016-012237.supp2supplementary appendix

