### Outcomes

#### Primary outcome measure

The primary outcome measure is DGF defined as the need for dialysis in the first 7 days post-transplantation.^18^

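### The primary model for dialysis-defined DGF omits recipients' pretransplant dialysis status: a missed gain in precision, not an error

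*Protocol article*

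**What the plan says.** Four places in the protocol article bear on this.

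- Outcomes, Primary outcome measure: "The primary outcome measure is DGF defined as the need for dialysis in the first 7 days post-transplantation".
- Eligibility: besides a DCD category III or IV transplant, "the donor and recipient must be ≥18 years and it must be the patient's first or second kidney transplant". The exclusions are donor or recipient age, other DCD categories, third or later transplants, multiorgan transplants, and "patients receiving dual kidney transplants, paediatric en-bloc kidney transplants or kidneys that have been preserved by hypothermic machine perfusion". Nothing requires the recipient to be on dialysis, and nothing excludes a recipient who is not.
- Primary analysis: the numbers with DGF "will be compared using a logistic regression model adjusting for cold ischaemic time and donor age". Both covariates describe the donor or the organ.
- Randomisation: "Patients will be allocated at random in a 1:1 ratio". For pairs transplanted in one centre, "one kidney from the pair will be randomly allocated to CS and the other to EVNP". Splitting pairs balances donor factors within the pair but not the recipients' dialysis status.

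The section on analysis of outcomes defers detail to a full statistical analysis plan, due before the first interim analysis. The primary model's covariates are nevertheless named, so this point concerns a stated choice and not a gap left for that plan.

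**The concern.** The outcome is a treatment given to the recipient, so it depends on the recipient's own kidneys as well as on the graft. Someone whose native function sufficed without dialysis before surgery may get through a week of slow graft function undialysed. Someone without that reserve, given the same graft, is more likely to be dialysed and counted as DGF. That the first group has the lower risk is an inference from the definition; the article gives no figure for it.

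If the inference is right, dialysis status is a prognostic factor known at admission and unaffected by allocation. A logistic model that includes such a factor usually has more power for the treatment effect, and its estimate is protected when the factor happens to be unevenly spread between arms. Cold ischaemic time and donor age do not capture it.

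**Working it through.** **Inputs from the article (Sample size determination).** "the overall rate of DGF in DCD kidney transplants is 50"%; "30% relative reduction in DGF (from 50% to 35%) with a power of 80% and a statistical significance of α=0.05"; 376 evaluable patients, taken as 188 per arm; 6% withdrawal; 400 recruited. Two-sided testing is assumed.

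**Reproducing the stated size.** Per arm, n = [1.960·√(2 × 0.425 × 0.575) + 0.842·√(0.50 × 0.50 + 0.35 × 0.65)]² / 0.15² = 169.3, so 170 per arm and 340 in total. With a continuity correction it is 183 per arm and 366 in total, within 3% of the stated 376. And 376 / 0.94 = 400.

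**Inputs assumed.** s is the pre-emptive share and q is its DGF rate under cold storage. The article gives neither, so both are varied. Overall rates are held at 50% and 35%, with one odds ratio common to both recipient groups. The two planned covariates and the pairing are left out.

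**Power without the covariate.** The log odds ratio is ln(0.35/0.65) − ln(0.50/0.50) = −0.619. Its standard error is √[1/(188 × 0.25) + 1/(188 × 0.2275)] = 0.2113. The ratio is 2.929, and power is Φ(2.929 − 1.960) = 83.4%.

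**Power with it, worked for s = 20%, q = 15%.**

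- Cold-storage DGF among recipients on dialysis: (0.50 − 0.20 × 0.15) / 0.80 = 58.75%.
- The common log odds ratio that gives 35% overall in the EVNP arm is −0.688. The EVNP rates become 8.15% and 41.7% (check: 0.20 × 0.0815 + 0.80 × 0.417 = 0.350).
- Information in each group is v₀v₁/(v₀ + v₁), with v = 188 × group share × p(1 − p). Pre-emptive: 4.79 and 2.81 give 1.77. On dialysis: 36.45 and 36.57 give 18.25. The sum is 20.03, so the standard error is 0.2235.
- The ratio is 3.08, and power is Φ(3.08 − 1.96) = 86.9%, a gain of 3.5 points.

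The same formula over a grid gives this power with the covariate, to set against 83.4% without it:

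| Pre-emptive share | q = 5% | q = 10% | q = 20% | q = 30% |
|---|---|---|---|---|
| 5% | 84.5% | 84.3% | 83.9% | 83.6% |
| 10% | 85.8% | 85.4% | 84.5% | 83.9% |
| 15% | 87.3% | 86.5% | 85.2% | 84.2% |
| 20% | 88.9% | 87.8% | 86.0% | 84.6% |
| 25% | 90.6% | 89.3% | 86.9% | 85.0% |
| 30% | 92.5% | 90.9% | 87.9% | 85.5% |

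**Check by simulation (6,000 trials per scenario).** Power without and then with the covariate was 84.4% and 85.1% (s = 10%, q = 10%), 84.8% and 87.3% (15%, 10%), 84.6% and 89.4% (25%, 10%), and 84.6% and 87.7% (25%, 20%). Under no effect, rejection rates were 3.9-5.0% without the covariate and 4.4-5.5% with it. Under the planned effect, the two models disagreed on significance in about 4-8% of trials.

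**Chance imbalance, s = 20%, q = 15%.** The SD of the between-arm difference in share is √(2 × 0.20 × 0.80 / 188) = 4.1 points. Multiplied by the risk gap of 58.75 − 15 = 43.75 points, a 1-SD imbalance moves the crude DGF difference by 1.8 points and a 2-SD imbalance by 3.6. The gap in the EVNP arm is smaller (41.7 − 8.15 = 33.6 points), so these figures lean high. The standard error of the difference is √(0.25/188 + 0.2275/188) = 5.0 points, so the 1-SD shift is about 0.36 of a standard error.

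**The case against.** The strongest reply is that nothing here is wrong. Randomisation makes the two-covariate model valid, and the simulated type I error stays near 5% with or without the extra term. A reader might infer that the trial is underpowered. The figures do not support that: power without the covariate is above 80% throughout, and because the 50% control rate is an overall rate for DCD transplants, it presumably already includes any pre-emptive recipients. All of this stands. The loss is only relative to a more efficient model.

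Second, the size is assumed. At a 5% share the gain is negligible, and the larger gains need shares of 20-30%, which the article neither supports nor rules out. This also stands.

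Third, chance imbalance affects any omitted prognostic factor and is already reflected in the standard error. That is right, and it is why the shift should be read against 5.0 points and not only against the 15-point target.

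Fourth, the article concedes that dialysis-defined DGF is subjective, plans creatinine-based secondary outcomes, and will tabulate characteristics by arm. These help interpretation but do not change the primary estimate.

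Two further inferences go too far. The article does not show that the outcome cannot register graft function in pre-emptive recipients, only that its definition makes a lower rate plausible. Nor does the open-label design make a chance imbalance worse.

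What survives is narrow: a baseline factor linked to the outcome by definition is left out of a named covariate set, and including it costs almost nothing.

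**Conclusion.** The point holds as a recommendation to improve the primary model, not as an error in it. The planned test is valid and meets its stated 80% power.

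Adjusting for dialysis status would raise power by about 1 point or less at a 5% pre-emptive share (at most 1.2) and by about 1 to 4 points at 10-15% for q between 5% and 20%. At 20-30% the gain is about 3.5 to 7 points in mid-range scenarios: 3.5 at a 20% share with 15% DGF, and 7.5 at a 30% share with 10% DGF. Over the wider grid at 20-30%, it runs from 2.6 to 9.1 points for q between 5% and 20%, and falls to 1-2 points at q = 30%.

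These figures assume a lower week-1 dialysis rate in pre-emptive recipients, a common odds ratio, and overall rates of 50% and 35%. The unseen analysis plan may already contain the covariate, in which case only the article's statement of the model needs to be aligned with it.

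**What to change.** Before the first interim analysis, add on dialysis at transplantation (yes/no) to the primary logistic model as a prespecified third covariate, alongside cold ischaemic time and donor age. Leave eligibility unchanged. An analysis restricted to recipients on dialysis at transplantation would be a useful supportive addition, but it is optional.

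The cost is one baseline field, known at admission, and one model term; no extra patients or procedures are needed. The one statistical consequence to state is that the odds ratio becomes conditional on one more factor and typically lies further from 1. In the worked scenario it is 0.50, against an unadjusted (0.35/0.65) / (0.50/0.50) = 0.54 for the same 50% and 35%. Reporting the DGF percentages by arm beside it avoids misreading.

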**Methods and analysis:**

This is a UK-based phase II multicentre randomised controlled trial to assess the efficacy of EVNP compared with the conventional static cold storage technique in donation after circulatory death (DCD) kidney transplantation. 400 patients receiving a kidney from a DCD donor (categories III and IV, controlled) will be recruited into the study. On arrival at the transplant centre, kidneys will be randomised to receive either EVNP (n=200) or remain in static cold storage (n=200). Kidneys undergoing EVNP will be perfused with an oxygenated packed red cell solution at near body temperature for 60 min prior to transplantation. The primary outcome measure will be determined by rates of delayed graft function (DGF) defined as the need for dialysis in the first week post-transplant. Secondary outcome measures include incidences of primary non-function, the duration of DGF, functional DGF defined as <10% fall in serum creatinine for 3 consecutive days in the first week post-transplant, creatinine reduction ratio days 2 and 5, length of hospital stay, rates of biopsy-proven acute rejection, serum creatinine and estimated glomerular filtration rate at 1, 3, 6 and 12 months post-transplant and patient and allograft survival. The EVNP assessment score will be recorded and the level of fibrosis and inflammation will also be measured using tissue, blood and urine samples. Ethics and dissemination. The study has been approved by the National Health Service (NHS) Health Research Authority Research Ethics Committee. The results are expected to be published in 2020.

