### Postperfusion

After EVNP, kidneys will be flushed with ∼500 mL of cold (4^°^C) HOC (Baxter Healthcare, UK) to remove the perfusate and then placed back in ice until transplanted. Prior to transplantation, the arterial Carrel patch may have to be excised along with a short segment of vein in order to remove the cannula ligature sites.

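### The primary DGF model adjusts for cold ischaemic time without limiting it to time before randomisation; total cold time can be changed by allocation, so using it may distort the odds ratio in either direction

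*Protocol article*

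**What the plan says.** Protocol article, Primary analysis: the DGF counts "will be compared using a logistic regression model adjusting for cold ischaemic time and donor age". Neither this section nor any other defines cold ischaemic time or says how an EVNP kidney's warm hour and second cold period are counted.

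The sequence of events is spread over several sections:

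- Randomisation: "Randomisation will be performed after the transplant recipient and kidney have both arrived in the transplanting centre", once the decision to go ahead with the transplant is final.
- Abstract, Methods and analysis: control kidneys stay in static cold storage. EVNP kidneys are perfused "at near body temperature for 60 min prior to transplantation".
- Postperfusion: after EVNP the kidney is flushed with cold solution "to remove the perfusate and then placed back in ice until transplanted".
- Analysis population and principles: the primary efficacy analysis is by intention to treat.
- Analysis of primary and secondary outcomes: a full statistical analysis plan will follow before the first interim analysis; the article gives the main points.

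**The concern.** A covariate in the primary model of a randomised trial should be fixed before allocation or be unaffected by it. Cold time up to randomisation meets that condition. Total cold time to implantation need not, because the clock is still running at allocation and EVNP acts directly on what follows: it replaces some cold time with warm perfusion, may postpone implantation, and adds a second cold period.

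The question is whether adding EVNP to cold storage, with its effect on timing, reduces DGF. If EVNP changes total cold time and cold time affects DGF, holding total cold time constant removes that part of the net effect. Where EVNP lengthens cold time, the model discounts a harm and makes EVNP look better. Where EVNP shortens it, the model discounts a benefit and makes EVNP look worse. All randomised patients would still be analysed in their allocated arm, but the contrast would no longer be the total effect of allocation.

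A second route to distortion is a factor that affects both post-randomisation delay and DGF. The vascular complexity described under Multiple vessels is a plausible example, though the article does not document such a link.

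**Working it through.** **Inputs from the article** (Sample size determination): DGF 50% v 35%, "with a power of 80% and a statistical significance of α=0.05", 376 patients, 400 after 6% withdrawal. Sidedness is not stated; two-sided is assumed.

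**The plan's own figure.** The two-proportion formula with pooled variance gives [1.960 × √(2 × 0.425 × 0.575) + 0.842 × √(0.50 × 0.50 + 0.35 × 0.65)]² / 0.15² ≈ 169.3, so 170 per arm and 340 in total. With continuity correction it is 183 per arm, 366 in total, within 3% of 376. 376 / 0.94 = 400. The sample size is not in dispute; it supplies the effect size.

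**Design effect.** Odds ratio = (0.35/0.65) / (0.50/0.50) = 0.538; log odds ratio = -0.619. Standard error at 188 per arm = √[1/(188 × 0.25) + 1/(188 × 0.2275)] ≈ 0.21.

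**Size of the distortion.** If EVNP changes total cold time by s hours and each hour multiplies the odds of DGF by h, then

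log odds ratio adjusted for total cold time ≈ total effect - s × log(h).

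The article gives neither s nor h. Assumed ranges: h from 1.02 to 1.08 (log h from 0.020 to 0.077), and s of -1, 0, +1 or +2 h.

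The formula was checked by simulating 1,000,000 patients per scenario with the net effect held at the planned value. Further assumptions were pre-randomisation cold time with mean 12 h and SD 4 h, post-randomisation variation with SD 1.5 h, and a modest donor-age effect. Adjusting for pre-randomisation cold time returned an odds ratio of about 0.54 throughout. Adjusting for total cold time gave:

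| Shift s | Simulated move in log odds ratio | Odds ratio | Relative to the planned effect |
|---|---|---|---|
| -1 h | +0.020 to +0.075 | 0.55 to 0.58 | diluted 3 to 12% |
| 0 h | about 0 | about 0.54 | no change |
| +1 h | -0.020 to -0.077 | 0.53 to 0.50 | exaggerated 3 to 13% |
| +2 h | -0.039 to -0.155 | 0.52 to 0.46 | exaggerated 6 to 25% |

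By hand, the extreme case is 2 × 0.077 = 0.154, and 0.154 / 0.619 = 25%.

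**With an unmeasured common cause.** Adding a factor that lengthens the delay by 1 h per SD and raises the log-odds of DGF by 0.5 per SD widened the range to 15% dilution (-1 h) and 37% exaggeration (+2 h). At zero shift the change was at most 2%. This is a further assumption.

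**What it could do to the test.** If EVNP had no net effect but lengthened cold time, a move of 0.02 to 0.155 is 0.10 to 0.74 standard errors. The chance of a significant result favouring EVNP would rise from 2.5% to between P(Z < -1.86) ≈ 3% and P(Z < -1.22) ≈ 11%.

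**Is a zero shift likely?** If the warm hour is counted as cold time, the recorded total is unchanged only if EVNP fits inside waiting time that would have passed anyway. If it is not counted, the total is unchanged only if implantation is delayed by as much as the time left out. Zero shift is possible but is a special case, and the article does not say which applies.

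**The case against.** The strongest reply is that the article never says cold ischaemic time runs to implantation. Ended at arrival or at randomisation, it is an ordinary baseline covariate and there is no problem. The article defers detail to an analysis plan that is not shown, and covariate definitions are often settled there. It also documents no between-arm difference in cold time, and the distortions computed without added confounding are all below one standard error, in unknown direction.

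Much of this stands, and it limits what can be claimed. A reader might infer that the primary estimate is biased, or that it flatters EVNP. The documents support neither, because they give no end point for the covariate, no shift and no hourly effect on DGF.

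A reader might also cite the rule that, for paired kidneys in one centre, "the randomisation will also determine which kidney (right or left) will be transplanted first". That shows cold time is still accruing at allocation, but the article does not say that order is tied to arm. If order is independent of arm, the resulting cold-time differences balance out and do not bias the comparison.

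The reply does not dispose of the point. The article names the covariate for the primary model rather than leaving it open. An analysis plan that followed that wording using total time to implantation would adjust for something the intervention can change.

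**Conclusion.** The point holds conditionally. The covariate is not restricted to time before randomisation, and the trial's own sequence makes total cold time a quantity that allocation can alter. If total cold time is used, the adjusted odds ratio is not the total intention-to-treat effect on DGF and may be distorted either way.

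Under the assumed 1.02 to 1.08 per hour and -1 to +2 h, the size is small to moderate, and these ranges are illustrations rather than estimates for this trial. The true direction and size cannot be determined from the article. Because the ambiguity sits in the confirmatory analysis and is cheap to remove, it should be settled before the first interim analysis.

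**What to change.** In Primary analysis and in the statistical analysis plan, define the covariate as cold time from the start of cold flush or storage at retrieval to randomisation, or to arrival at the centre if randomisation time is not recorded. Keep donor age. State how the EVNP hour is counted. Report total cold time by arm, with its pre-EVNP and post-EVNP parts in the EVNP arm, as a process measure. Use total cold time as a covariate only in a supportive analysis labelled as such.

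The cost is a change of wording, provided the flush, arrival, randomisation, EVNP and implantation times are on the electronic case report form; the article does not list its fields, so this needs checking. Pre-randomisation cold time may explain somewhat less outcome variation than total cold time, so a little precision may be lost; the amount cannot be estimated from the article. The sample size does not change.

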### Immunosuppressive therapy

All centres will use similar immunosuppressive protocols as follows: patients will receive 20 mg of basiliximab intravenously pretransplant and 20 mg intravenously on postoperative day 4. Patients will receive a bolus of methylprednisolone intravenously at induction of anaesthesia using a dosage according to local practice. The post-transplant oral prednisolone regimen will also be according to local practice.

Patients may be treated with either tacrolimus or cyclosporine according to local protocols. There will be no restriction on the formulation of the prescribed calcineurin inhibitors. Tacrolimus will be prescribed to achieve target trough levels of 3–12 ng/mL. Cyclosporine will be prescribed to achieve target trough levels of 100–250 ng/mL. The first dose of calcineurin inhibitor may be given preoperatively or postoperatively. All patients will receive mycophenolate as either mycophenolate mofetil (Cellcept) at a starting dose of at least 1 g/day or mycophenolate sodium (Myfortic) starting at a dose of at least 720 mg/day.

Antimicrobial and antithrombotic prophylaxis will be given according to local protocols. It is expected that patients will also receive prophylaxis against *Pneumocystis jirovecii* pneumonia, oral candidiasis and cytomegalovirus (valganciclovir for 100 days in CMV-positive donor to CMV-negative recipient transplants).

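### The primary logistic model leaves out centre; adding it costs almost nothing and recovers a small amount of power

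*Protocol article*

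**What the plan says.** Under Primary analysis, the protocol article states that the numbers with DGF will be compared between arms by logistic regression, "adjusting for cold ischaemic time and donor age". No other covariate is named. The section Analysis of primary and secondary outcomes describes this as a summary: "The analyses will be described in detail in a full statistical analysis plan", to be drawn up before the first interim analysis.

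The parts of the article that bear on centre are these:

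- Eligibility: "There will be four participating centres in the UK".
- Randomisation: "Patients will be allocated at random in a 1:1 ratio", with no mention of stratification by centre. When both kidneys of a donor go to one centre, "one kidney from the pair will be randomly allocated to CS and the other to EVNP". Nobody is blinded.
- Strengths and limitations: DGF defined by dialysis is acknowledged to be subjective.
- Immunosuppressive therapy: the centres' protocols are described as similar and several elements are common to all. However, "Patients may be treated with either tacrolimus or cyclosporine according to local protocols", and steroid dosing is also left to local practice.
- Sample size determination: one overall DGF rate of 50%, from five years of data. No rate by centre is given.

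**The concern.** The endpoint records a clinical decision to dialyse, made by staff who know the allocation, in four hospitals that differ in part of their immunosuppression. It is reasonable to expect the DGF rate to vary somewhat between centres. A factor that predicts the outcome and is known at randomisation is a natural covariate, and centre is recorded in any case.

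In logistic regression, omitting such a factor moves the treatment odds ratio towards 1 and reduces the power to detect a real effect. If the arms happen to be unevenly spread over the centres, nothing in the named model corrects for it. The trial was planned at 80% power, so the question is how much of that is given away.

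**Working it through.** **1. The plan's own sample size.** Inputs from Sample size determination: 50% v 35%, power 80%, α = 0.05 (taken as two-sided).

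n per arm = [1.96·√(2·0.425·0.575) + 0.8416·√(0.25 + 0.2275)]² / 0.15² = (1.370 + 0.582)² / 0.0225 ≈ 169.3, so 170 per arm and 340 in total. With the Fleiss continuity correction this becomes 183 per arm, or 366. Inflating by about 1.017 for two O'Brien-Fleming interim looks gives 366 × 1.017 ≈ 372. The stated 376 is within 3% of the last two figures. The withdrawal allowance is exact: 376 / 0.94 = 400. Nothing in this calculation involves centre. Without the continuity correction, 188 per arm gives about 84% power, which is the baseline for what follows.

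**2. Simulation set-up.** N = 376 and four centres of equal expected size. The treatment log odds ratio within centre is ln[(0.35/0.65)/(0.5/0.5)] = −0.619. One standard-normal covariate stands in for cold ischaemic time (log odds ratio 0.2 per SD), and there is no donor-age term. Single kidneys are allocated without regard to centre, so chance imbalance is already in the results. Either none or half of the kidneys come from same-centre pairs split between arms. There are 2,000 trials per scenario, each analysed with and without centre. The centre rates, covariate effect, centre sizes and pair share are assumptions.

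**3. Results without any donor effect.**

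| Control DGF by centre (%) | Kidneys in pairs | Power without / with centre | Gain (points) | Mean log OR without / with | Type I error without / with |
|---|---|---|---|---|---|
| 50/50/50/50 | 0% | 0.845 / 0.847 | 0.2 | −0.629 / −0.634 | 0.052 / 0.050 |
| 50/50/50/50 | 50% | 0.837 / 0.837 | 0.0 | −0.625 / −0.630 | 0.046 / 0.050 |
| 40/45/55/60 | 0% | 0.813 / 0.817 | 0.4 | −0.606 / −0.627 | 0.050 / 0.056 |
| 40/45/55/60 | 50% | 0.823 / 0.826 | 0.3 | −0.609 / −0.629 | 0.052 / 0.055 |
| 30/40/60/70 | 0% | 0.739 / 0.768 | 2.9 | −0.555 / −0.619 | 0.049 / 0.053 |
| 30/40/60/70 | 50% | 0.765 / 0.801 | 3.6 | −0.569 / −0.635 | 0.051 / 0.059 |
| 20/40/60/80 | 0% | 0.669 / 0.760 | 9.1 | −0.505 / −0.633 | 0.051 / 0.046 |
| 20/40/60/80 | 50% | 0.674 / 0.753 | 7.9 | −0.498 / −0.627 | 0.037 / 0.050 |

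Monte Carlo standard errors are about √(0.05·0.95/2000) = 0.005 for type I error and √(0.8·0.2/2000) = 0.009 for power. Both models are fitted to the same simulated trials, so the gains are more precise than the levels. As odds ratios, the 30–70% row without pairs reads e^−0.555 = 0.574 without centre and e^−0.619 = 0.538 with it.

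**4. Sensitivity.** With a strong donor effect (SD 1 on the logit scale) the gains are −0.7 to 0.1 points with no centre spread, 0.9 to 1.4 at 40–60% and 2.5 to 2.9 at 30–70%. A differently calibrated set of 3,000 trials, with two other moderate covariates and centre log-odds effects of −0.8, −0.25, 0.25 and 0.8 (rates about 31% to 69%), gave 85.6% without centre and 87.9% with it, a gain of 2.3 points. With those effects halved it gave 86.0% and 86.5%, a gain of 0.5. The absolute level depends on calibration, but the small difference does not.

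**5. Cost in the model.** Expected events are 188·0.50 + 188·0.35 = 159.8, about 160, against three extra parameters.

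**The case against.** The strongest reply is that this is detail for the SAP. The article says that it summarises, and the SAP, which is not shown, may add centre. That is fair as far as it goes. However, the article does not leave the covariate set open: it names two covariates, and centre is not one of them. The suggestion changes a stated method and does not fill a gap.

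The second reply is that the gain is small and centre differences are unproven. This stands. The article describes the centres' immunosuppression as similar, with common basiliximab dosing, trough targets and mycophenolate minimum doses. It gives no DGF rate by centre. The loss of 8 to 9 points needs a spread of 20% to 80%, which nothing in the article supports.

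A reader might also draw stronger conclusions that the article does not bear out:

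- *That dialysis practice is local.* The article says only that the endpoint is subjective. Different thresholds by centre are an inference.
- *That splitting pairs within centre calls for a centre term.* The correlation it raises is between two kidneys of one donor. With half the kidneys paired and a strong donor effect, type I error was 0.028–0.043 without centre and 0.033–0.044 with it, so a centre term does not deal with that.
- *That the standard error is materially wrong.* Even with full balance within centre, which the article does not state, the model standard error (0.212–0.219) exceeded the empirical SD (0.207–0.212) by only about 2–3%. Adding centre to a logistic model raises the reported standard error, from 0.212 to about 0.224. The power gain comes from the less attenuated odds ratio.
- *That every outcome analysis should include centre.* The secondary analyses are mostly Fisher's exact, t and log-rank tests, which take no covariate. Including centre there would mean replacing or stratifying them.

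**Conclusion.** The point holds as a modest improvement to a stated method. Without centre the primary comparison remains valid. Type I error without centre was 0.037–0.052 with no donor effect. The one higher value among the donor-effect runs (0.060) arose where the centres were identical and was 0.064 with centre included, so omitting centre did not cause it. The odds ratio without centre is averaged over centres and lies nearer to 1. It answers a slightly different question and is not an error.

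The loss is about 0 to 1 point of power if control rates span about 40–60%, and about 2 to 4 points at about 30–70%. If the centres are alike there is no material loss from including the term. These sizes rest on assumed centre rates, equal expected centre sizes and a within-centre odds ratio of 0.538.

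A reader might infer from power values such as 0.74 in the table that the trial is underpowered. That would be wrong: those levels follow from holding the within-centre odds ratio fixed while widening the spread. Only the difference between the two models bears on this point.

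**What to change.** Add centre as a four-level fixed factor to the primary logistic model, beside cold ischaemic time and donor age, or give a reason for leaving it out. Record the choice in the SAP before the first interim analysis, so that in an unblinded trial it cannot appear to follow from the data. The sponsor could judge the likely gain from the five years of centre data behind the 50% rate.

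The cost is three degrees of freedom against about 160 expected events, and an odds ratio conditional on centre as well as on the two covariates already named. No extra data are needed and the sample size does not change. The recommendation is confined to the primary model. How to account for donor pairs is a separate matter that this change does not settle.
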